## Abstract

**Background:**

Long COVID-19 is a medical condition associated with persistent physical, cognitive, and emotional symptoms. Despite its significant impact, there are still few psychological interventions—especially with transdiagnostic approaches— that have been rigorously tested in this population. The aim of the present protocol is to describe a randomized controlled trial to examine the effectiveness and acceptability of the online, group-delivered Unified Protocol (UP) for improving emotional, and cognitive outcomes in adults with long COVID-19. We expect greater improvements in emotional and cognitive outcomes for the UP group compared to controls. Additionally, exploratory analyses will assess changes in neurocognitive performance and hair cortisol/cortisone levels as potential correlates of treatment response.

**Methods:**

90 individuals diagnosed with long COVID-19 will be randomized to an experimental group or a waiting-list control group (1:1 ratio). Participants in the experimental group will receive the UP across 12 online group sessions. Longitudinal assessments (pre-treatment, post-treatment and 3, 6 and 12 months follow-ups) will include psychological (e.g., anxiety and depressive symptoms) and cognitive outcomes (e.g., memory failures). Participants in the experimental group will also complete neuropsychological tests and will provide hair samples for the assessment of cortisol/cortisone levels.

**Data analyses:**

Baseline characteristics will be described using descriptive statistics, and linear mixed-effects models will evaluate the effects of time, group, and their interaction on psychological and cognitive outcomes. Neuropsychological performance and hair cortisol levels will be analyzed over time in the experimental group. Associations between cortisol and psychological or cognitive measures will be explored through correlational analyses.

**Conclusions:**

We expect positive outcomes after the intervention in acceptability and in emotional symptoms and cognitive complaints in individuals living with long COVID-19, the maintenance of the benefits in all follow-ups, and statistically significant changes in favor of the UP condition in comparison with the waiting-list control group. If effective, the UP could provide an accessible and evidence-based psychological treatment for this population, improving the quality of healthcare to individuals with long COVID-19.

**Trial registration:**

clinicatrials.gov (registration identifier: NCT06928480; May 22, 2025).

## Introduction

The World Health Organization (WHO), a global leader in the study and management of public health emergencies, has been committed, since the beginning of the COVID-19 pandemics, to studying not only the acute symptomatology but also the evolution of individuals affected by the SARS-CoV-2 virus. As early as September 2020 the term “post COVID condition” was included in one of the main diagnostic medical tools worldwide, the International Classification of Diseases [ICD-10 code (U09)]. This diagnostic criteria was made by the WHO to distinguish between acute infection, late effects, and prolonged COVID-19 disease [1]. However, the complete definition of this condition was not formally established until October 2021, as stated below:

Post COVID-19 condition occurs in individuals with a history of probable or confirmed SARS CoV-2 infection, usually 3 months from the onset of COVID-19 with symptoms and that last for at least 2 months and cannot be explained by an alternative diagnosis. Common symptoms include fatigue, shortness of breath, cognitive dysfunction but also others and generally have an impact on everyday functioning. Symptoms may be new onset following initial recovery from an acute COVID-19 episode or persist from the initial illness. Symptoms may also fluctuate or relapse over time [2].

Clearly defining the medical profile of patients with long COVID can be challenging, as more than 200 symptoms have been described [3], making it a condition with substantial heterogeneity in its clinical manifestations. A recent systematic review and meta-analysis including 36 studies with long COVID-19 patients and more than 11.000 participants revealed the presence of general (e.g., pain, fatigue, fever, hair fall, skin rash, weight loss), neurological (e.g., headache, cognitive impairment, loss of smell, taste and hearing), cardiopulmonary (e.g., chest pain, sore throat, dyspnea, palpitations and cough), and gastrointestinal symptoms (e.g., poor appetite, diarrhea, nausea, abdominal pain) [4]. Similarly, variations in the prevalence of this condition has been exposed, but currently it has been estimated that 6 in every 100 people who have been infected with COVID-19 develop post COVID-19 (or long covid) condition [2].

Apart from the WHO, other internationally recognized organizations have also acknowledged the relevance of the long COVID-19 condition and the urgency of addressing it promptly. Thus, the European Network of expertise on Long COVID-19 from the European Commission [5], the Center for Disease Control and Prevention (CDC) from the United States [6] or the National Institute for Health and Care Excellence (NICE) from United Kingdom [7] have postulated the need to better prevent and treat long COVID-19 conditions. However, it is also noteworthy that interest has usually focused on the physical recovery of symptoms instead of helping people with long COVID-19 to psychologically adapt to the illness and prevent or treat the emotional disorders that could emerge.

Psychological care for patients with long COVID-19 should not be neglected as numerous studies have shown that emotional suffering is markedly prevalent among these individuals. More precisely, a recent systematic review and meta-analysis including 143 studies and over 7 million participants has revealed that the prevalence of anxiety and depressive symptoms in patients with long COVID-19 is around 23% [8]. This alarming prevalence of emotional symptoms in patients with long COVID-19 has led to increased interest in developing and implementing psychological interventions for COVID-19 populations. However, a recent systematic review [9] have noted that intervention studies have primarily focused on acute COVID-19 patients, relatives and healthcare professionals, and to a lesser extent, on long COVID-19 patients. Furthermore, another recent systematic review [10] specifically examining interventions for individuals with long COVID-19, found that psychological support has not been a primary focus. Of the 31 included studies, only seven evaluated psychological interventions, whereas the remaining studies were centered on neurocognitive rehabilitation, natural supplementation, pharmaceutical treatments or physical rehabilitation programs [10]. A more detailed analysis of these seven psychological interventions shows that only two employed a rigorous methodological design as randomized controlled trial (RCT), and the therapeutic psychological approaches used are highly heterogeneous, including cognitive processing therapy, acceptance and commitment therapy, peer support or cognitive-behavioral therapy (CBT) [10]. Also importantly, although some participants included in the review presented comorbid anxiety and depressive symptoms (see the study by Skilbeck [11]) we also observed a lack of transdiagnostic approaches and a predominance of disorder-specific psychological interventions.

Even when CBT is one the psychological interventions with most accumulated evidence for adults with emotional disorders [12] and also populations with chronic physical conditions [13], focusing on specific cognitive-behavioral interventions for specific emotional disorders may present some important limitations. One major issue with applying disorder‑specific psychological programs — for example, a therapy designed only for depression — is that many patients present comorbidity, especially between anxiety and depressive symptoms [14], which limits the dissemination of single‑disorder treatments. The transdiagnostic approach — as embodied in the Unified Protocol (hereafter UP) — aims to overcome this limitation by targeting shared underlying processes (e.g., emotion dysregulation) across multiple emotional disorders [15]. Different RCT have demonstrated the non-inferiority of the UP as it achieves reductions in anxiety and depressive symptoms comparable to those produced by standard evidence-based single-disorder treatments [16,17]. Also importantly, the UP has demonstrated its usefulness in prevent or treat emotional disorders in individuals with medical health conditions [18]. Given the high rates of comorbidity and overlapping mechanisms in emotional disorders, transdiagnostic treatments like the UP may represent a more parsimonious and flexible solution for individuals with emotional disorders and long COVID-19 than multiple disorder‑specific interventions [19].

It is also important to note that emotional symptoms in long COVID do not appear to occur in isolation but are frequently accompanied by cognitive difficulties. Individuals with long COVID-19 show prevalence rates of cognitive complaints (particularly difficulties in memory and concentration) ranging from approximately 21% to 25%, which are comparable to those reported for anxiety and depressive symptoms (for a meta-analysis, see the study from van der Feltz-Cornelis [20]). Moreover, evidence from long COVID-19 population suggests that greater emotional symptomatology is associated with poorer cognitive performance [21]. Taken together, these findings underscore the importance of developing and evaluating psychological interventions targeting emotional symptoms in individuals with long COVID, in order to examine whether improvements in emotional functioning are accompanied by benefits in cognitive performance, an area that remains largely unexplored in the current literature.

With all this information in mind, the primary aim of this RCT is to assess the effectiveness and acceptability of the UP delivered in an online group format for treating emotional disorders in long COVID-19 patients. We hypothesize that participants in the experimental group will show improvements in psychological and cognitive outcomes. Specifically, we expect that at post-treatment participants in the experimental group will exhibit reductions in depressive and anxiety symptoms, memory failures, dimensions of emotional disorders (neuroticism, depressed mood, somatic anxiety, arousal activation, social anxiety, intrusive cognitions, traumatic re-experiencing and avoidance), difficulties in emotion regulation and perceived stress. In addition, we anticipate increases in quality of life, distress tolerance and positive temperament scores. We expect these improvements to be maintained at follow-up assessments conducted 3, 6 and 12 months after the intervention. We further hypothesize that participants in the experimental group will show greater improvements in psychological and cognitive outcomes compared to those in the control group. Additionally, the study will examine participant acceptability and satisfaction with the UP intervention and the online group format of delivery, with expectations of high satisfaction and adherence rates.

The secondary aim of this study is to explore the evolution of neurological, cognitive and physiological outcomes in a sample of long COVID-19 patients. Longitudinal changes in cognitive impairments (i.e., visuospatial skills, memory, working memory, attention, concentration, language, executive functions, orientation and verbal short-term memory), cortisol and cortisone levels will be measured in the experimental group to investigate potential neurological and physiological correlates of the UP intervention. To the best of our knowledge, no studies have explored the usefulness of the UP in reducing cognitive impairments or cortisol/cortisone levels in long COVID-19 patients. Consequently, this aspect of the study is exploratory in nature and no formal hypotheses are proposed.

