### Participants

Participants will be adults residing in the Autonomous Community of Aragon (Spain) who have been diagnosed with long COVID-19 and meet criteria for at least one comorbid emotional disorder. Recruitment will take place at Hospital Royo Villanova from Zaragoza, Spain. An online dissemination campaign will also be conducted through social medial and in collaboration with the Long COVID-19 association from Aragón. Eligibility criteria to participate in the study are reported in Table 1. Participants will not be involved in the design, conduct or reporting the trial.

**Table 1 pone.0342908.t001:** Inclusion and exclusion criteria to participate in the randomized controlled trial.

Inclusion criteria	Exclusion criteria
Residing in the Autonomous Community of Aragon (Spain). Being at least 18 years old. Understanding of Spanish. Being diagnosed with long COVID-19: documented SARS-CoV-2 infection and persistence of symptoms beyond 12 weeks after the acute infection. Symptoms of depression (ODSIS≥7) and/or anxiety (OASIS≥8). Meeting the criteria for an emotional disorder diagnosis. Having access to the Internet. Signing the informed consent.	Pre-existing emotional symptoms prior to the acute SARS-CoV-2 infection. Currently receiving psychological treatment. Having a diagnosis of severe mental disorder (e.g., personality disorder, bipolar disorder, etc.). Active suicidal ideation at the time of the assessment. Individuals on psychotropic medication must maintain their dosage throughout the study, unless medically contraindicated.

Using the G*Power software [23], and taking into account the two study conditions, the five assessment points (pre-treatment, post-treatment, and follow-ups at 3, 6, and 12 months), as well as the statistical models planned for data analysis, we calculated a total sample size of 74 participants, achieving a statistical power of 90%, an alpha level of 0.05, and an effect size of 0.30. Considering an anticipated dropout rate of 20%, the required sample size is estimated at 45 participants per condition (total sample size = 90 participants).

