### Procedures

All procedures described in this study were approved by the Ethics Committee of the Autonomous Community of Aragón. Changes to this original study protocol (current protocol version number 2; May 2, 2025) will be communicated to the aforementioned Ethics Committee for their approval.

Physicians and nurses working in the long COVID-19 unit will invite patients to participate in the study. Participants who are interested in the study will receive a document containing a QR code to access the online Qualtrics platform, where they can read and electronically sign the informed consent form. After signing the online document, participants will receive a numerical code to preserve their anonymity in subsequent online assessments, and will then complete the Overall Depression Severity and Impairment Scale (ODSIS; [24,25]) and the Overall Anxiety Severity and Impairment Scale (OASIS; [25,26]) to assess the presence of depressive and/or anxiety symptoms that helped the research team to determine whether they meet the initial eligibility criteria.

Participants who do not meet the ODSIS and OASIS criteria will receive an email thanking them for their interest in the study and informing them that they do not meet the initial eligibility criteria. In contrast, participants who meet the cutoff criteria for anxiety and depressive symptoms (ODSIS ≥ 7 and/or OASIS ≥ 8) will be contacted by telephone by the psychologist responsible for conducting the initial clinical interview and the subsequent psychological UP-based program. During this call, the psychologist will confirm that the participant is interested in taking part in the study and agrees to the conditions of the intervention (i.e., the possibility of being assigned to the waiting list control group, participation in the psychological intervention in an online group format, agreement with the assessment schedule, and provision of hair samples for cortisol/cortisone analysis). Once it is confirmed that the participant understands the study’s conditions and procedures, an online session via videoconference will be scheduled to conduct a clinical interview to determine the presence of an emotional disorder.

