After confirming the presence of at least one emotional disorder according to the Anxiety and Related Disorders Interview Schedule for DSM 5 (ADIS-5; [27]), participants will complete the online pre-treatment assessment protocol and will then be informed by email of their group assignment (either the experimental or the waiting list control group). Randomization to the experimental or group condition will be conducted by an independent researcher who will consult the pre-generated randomization sequence. The psychologist will also be informed of the assigned group to facilitate the management and organization of the UP-based experimental group intervention.

Participants in the experimental group will be required to complete an in-person additional assessment before they can begin the program. Accordingly, individuals assigned to the experimental group will meet in Zaragoza with a member of the research team to complete the neuropsychological and cognitive tests and to provide a hair sample for subsequent cortisol/cortisone analysis (secondary objective of this study). After these assessment point, participants will receive the UP-based psychological intervention in 12 online group sessions, each lasting 2 hours. Given that long COVID-19 patients often report cognitive difficulties [28] a break of approximately 10 minutes will be scheduled midway through each session. After the intervention, participants will complete the online post-treatment assessment protocol, which will include the measures administered at pre-treatment and a satisfaction questionnaire. Follow-up online assessments will also be conducted at three, six and twelve months after the intervention. At these time points, a group online session will be scheduled to monitor progress and reinforce the emotion regulation skills learned during the UP psychological program. At the three and twelve-month follow-up assessments, participants will repeat the in-person assessment to complete the neuropsychological and cognitive tests and to provide the hair samples for cortisol/cortisone analyses. Participants will receive email reminders for these appointments.

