#### Primary outcomes: Online survey assessment.

Overall Depression Severity and Interference Scale (ODSIS) [24,25]: depressive symptoms are assessed across five items evaluating frequency, intensity, severity, and interference of symptoms. Scores range from 0 to 20 points, with higher scores denoting greater depressive symptoms severity. While the Spanish validation of the questionnaire established a cutoff score of 10 points [25], in this study, and similar to previous research [29], the cutoff has been reduced to 7 points to ensure that all participants who may be experiencing depressive symptoms are thoroughly assessed for eligibility and can benefit from the psychological intervention. Thus, ODSIS cut-off was established at approximately half standard deviation below the mean scores obtained in the Spanish validation of this questionnaires (mean=9.87, *SD*=5.14) [25].Overall Anxiety Severity and Interference Scale (OASIS) [25,26]: this instrument measures anxiety symptomatology across five items assessing frequency, intensity, severity, and interference of symptoms. Total scores vary from 0 to 20 points; higher values indicate more severe anxiety symptoms. As explained in the section describing the depression questionnaire (ODSIS), in this study the cutoff score for the OASIS has been reduced to 8 points, taking into account the mean and standard deviation reported in the Spanish validation (mean=10.45, SD=4.49) [25]. This threshold corresponds to approximately half standard deviation below the Spanish mean, a criterion that allows participants with subclinical anxiety symptoms to be assessed and, if they met criteria for an emotional disorder, to participate in the study.

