### Data analysis

First, descriptive statistics of clinical psychological diagnosis, sociodemographic, and long COVID-19 symptoms will be explored to characterize the sample at baseline. Means and standard deviations for psychological measures (i.e., ODSIS, OASIS, etc.) at pre-treatment will also be calculated to provide a baseline description of our sample.

Second, the main effect of time, group and time x group interaction will be analyzed. Several linear mixed-effects models will be employed for each dependent variable to be analyzed (i.e., primary outcomes such as anxiety and depressive symptoms; secondary outcomes such as memory failures, emotional regulation difficulties, etc.). For each of these models, Time (within-subject variable; T1 vs. T2 vs. T3 vs. T4 vs. T5) and Experimental Group (between-subject variable; Experimental vs. Waitlist) will be included as fixed effects. Random slopes for participants will also be considered and included as random effects in the model. The models will have the following structure: [Dependent Variable ~ Time × Experimental Group + (1|Participant)].

In participants from the experimental group, descriptive analyses will also be conducted to assess their neuropsychological and cognitive status, as well as stress levels (hair cortisol and cortisone), prior to starting the intervention. Repeated measures ANOVAs with time as the within-subject factor will be performed to determine whether changes occur in these variables over time (i.e., after the intervention and at 3 and 12-months follow up). Exploratory correlational analyses will be conducted to examine associations between hormonal levels and other dependent variables. Subsequently, multiple linear regression analyses will be performed to determine which hormonal variables significantly predict subjective cognitive complaints, objective cognitive performance, and emotional variables, while controlling for relevant covariates (e.g., age and educational level).

Satisfaction with the intervention will be summarized using means and standard deviations derived from the satisfaction questionnaire. Additionally, adherence to the intervention will be calculated as the proportion of attended sessions relative to those scheduled.

Analyses will be conducted using the lme4 package (version lme4_1.1–13; [46]) in R statistical software (version 4.1.0; [47]) and SPSS v25.0 [48].

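### The entry scales are also the primary outcomes, so a fall within the UP arm, or a main effect of time, should not count as evidence of effectiveness; only the randomised comparison at T2 should

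*Protocol article*

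**What the plan says.** Table 1 of the protocol article requires "Symptoms of depression (ODSIS≥7) and/or anxiety (OASIS≥8". Under Procedures, these scales are completed at consent, and "participants who meet the cutoff criteria for anxiety and depressive symptoms (ODSIS ≥ 7 and/or OASIS ≥ 8) will be contacted by telephone". The diagnostic interview follows, after which "participants will complete the online pre-treatment assessment protocol and will then be informed by email of their group assignment". The Primary outcomes section then names ODSIS and OASIS as the two primary outcomes.

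The aims paragraph of the Introduction gives its expectations in order. First, "we expect that at post-treatment participants in the experimental group will exhibit reductions in depressive and anxiety symptoms". Next, these improvements are to be maintained at 3, 6 and 12 months. Only then comes a further hypothesis of greater improvement than in controls. The Conclusions of the Abstract make the same three-part list: positive outcomes after the intervention, benefits maintained at all follow-ups, and significant differences in favour of UP over the waiting list.

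The Data analysis section says that "the main effect of time, group and time x group interaction will be analyzed". The limitations in the Discussion acknowledge that only the experimental group is available after post-treatment. They do not mention regression to the mean.

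**The concern.** When people are admitted because a score passed a threshold on one occasion, their mean on that score tends to fall later without any treatment, as long as the correlation between occasions is below 1. Natural course can add to this. The waiting-list arm passes the same gate and should show the same fall from T1 to T2, but an expectation stated for the UP arm alone does not subtract it. A main effect of time does not subtract it either, because both arms' falls contribute to it. After T2 no control data exist, so every UP-arm change from T1 at 3, 6 and 12 months may contain the artefact with nothing to remove it.

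At stake is the interpretation. Two of the three stated expectations under effectiveness could be reported as met when UP does nothing.

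**Working it through.** **Inputs from the documents.** ODSIS: cut 7, validation mean 9.87, SD 5.14. OASIS: cut 8, "taking into account the mean and standard deviation reported in the Spanish validation (mean=10.45, SD=4.49". Planned n is 45 per arm with 20% dropout, so 45 × 0.80 = 36 completers.

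**Assumptions, not in the documents.** Screening-to-T2 correlation 0.6 to 0.7; ODSIS–OASIS correlation 0.6; mean of the source population equal to the validation mean or lower.

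**Step 1: the plan's own figure.** The protocol says "ODSIS cut-off was established at approximately half standard deviation below the mean scores obtained in the Spanish validation".
- ODSIS: (9.87 − 7)/5.14 = 0.56 SD below the mean.
- OASIS: (10.45 − 8)/4.49 = 0.55 SD below the mean.

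The statement is reproduced for both scales. The gate is therefore mild relative to that sample.

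**Step 2: one scale, one gate.** Expected fall with no effect = SD × φ(t)/(1 − Φ(t)) × (1 − r), where t = (cut − mean)/SD. For ODSIS, t = −0.558, φ(t) = 0.341 and 1 − Φ(t) = 0.712, so 5.14 × 0.341/0.712 = 2.46.
- r = 0.6: 2.46 × 0.4 = 0.99 points.
- r = 0.7: 2.46 × 0.3 = 0.74 points.

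**Step 3: the actual and/or rule.** People admitted on OASIS alone dilute the selection on ODSIS. Scores were simulated with zero treatment effect, rounded and clipped to 0–20, and selected if ODSIS ≥ 7 or OASIS ≥ 8. About 86% of a source population like the validation sample passes. The last column is the share of trials in which a UP-arm paired t test (two-sided 0.05, n = 36 to 45) shows a significant fall, against 2.5% nominal in that direction. The protocol does not specify this test for ODSIS or OASIS; it serves only as a yardstick.

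| Source population | T1 score | ODSIS fall, no effect | Significant fall |
|---|---|---|---|
| Validation mean | screening score | 0.3–0.4 | 7–10% |
| Validation mean | measured afresh | 0–0.3 | 2.5–7% |
| 1 SD lower | screening score | 1.0–1.3 | 33–52% |
| 1 SD lower | measured afresh | 0–0.8 | 2.5–23% |

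With source means of 5 (ODSIS) and 5.5 (OASIS) and the screening score as T1, the fall reaches about 1.4 points at r = 0.6. In the rows measured afresh, zero applies when all occasions correlate equally. The upper values apply when screening and T1 correlate at 0.85 to 0.9, more strongly than either does with T2 (0.6 to 0.7).

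**Step 4: the randomised contrast.** Both arms pass the gate before allocation, so the expected null falls are equal and cancel. If each arm falls by 0.4, the difference is (−0.4) − (−0.4) = 0. In simulation under the null, the two-sided between-arm test of ODSIS change rejected in 4.9% to 5.6% of trials, close to the nominal 5%.

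**The case against.** The strongest reply is that the trial's effectiveness test is already the controlled one. The Design section describes a superiority trial against the waiting list, the Introduction hypothesises greater improvement than in controls, and the Abstract's Conclusions end on that comparison. The planned model uses both arms, listing a time effect is ordinary reporting of a factorial model, and no passage says that the trial succeeds on a within-arm fall alone. This stands, and it confines the point to the within-arm, time-effect and follow-up claims. It does not remove the point, because the within-arm fall and its maintenance are still written as separate expectations under the effectiveness aim.

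Several points on size also stand.
- The cuts lie below the only documented means, so it is not accurate to say that participants must score high.
- The Data analysis section lists ODSIS and OASIS among the pre-treatment measures, which points to a fresh T1. The visible text does not settle this, and Fig 1 is not shown.
- The diagnostic interview is a second gate that the calculation leaves out. Confirmed cases may have a higher underlying mean, which would shrink the artefact.
- The Introduction's statement that "Symptoms may also fluctuate or relapse over time" concerns post-COVID symptoms in general. It makes a correlation below 1 plausible but gives no retest correlation for ODSIS or OASIS.

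The lack of a control group at follow-up is disclosed in the limitations. However, the Abstract and Introduction still call later UP-arm change benefits and improvements.

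**Conclusion.** The point holds in limited form. A fall in ODSIS or OASIS within the UP arm, its persistence at follow-up, and a main effect of time can all appear with no UP effect, so none of them is evidence of effectiveness by itself.

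On the only documented mean the artefact is small: about 0.3 to 0.4 ODSIS points with the screening score as T1, and 0 to 0.3 points with a fresh T1. It grows to about 1.4 points only if the source mean is as low as 5, which no passage states. All of these sizes rest on the assumed correlations.

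A reader might infer that the trial's main result is biased, or that false confirmation in about half of trials is to be expected. The documents support neither. The T2 comparison is randomised, hypothesised and unaffected, and the high rates need both an undocumented low source mean and a within-arm test that the protocol does not specify. The wording should be changed, but the trial is not invalidated.

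**What to change.** - In the Abstract's Conclusions, the aims paragraph of the Introduction and the Data analysis section, name the UP versus waiting-list difference at T2 (the time × group contrast from T1 to T2) as the sole confirmatory test of effectiveness.
- Report the UP arm's T1–T2 change beside the waiting-list change over the same interval, with confidence intervals.
- State that the main effect of time will not be used as evidence of efficacy.
- Describe UP-arm change at 3, 6 and 12 months as uncontrolled observed change that may include regression to the mean, and add this to the limitations.

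The cost is a few sentences and the notification to the Ethics Committee that the protocol already foresees for changes. No new data are needed, and it can be done before analysis, which is planned for after data collection ends. The small downside is giving up a within-arm significance claim.
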